## Abstract

**Background:**

Improving prognosis of BC patients has drawn the attention of health care professionals on disease related long-term side effects and on the multiple treatments BC patients must undergo. Despite advances in procedures, surgery still has multiple detrimental effects, including pain, edema, and limited mobility. For this reason, fostering adapted physical activity (APA) and healthy lifestyle (including a balanced diet and weight management) should become an everyday purpose of healthcare professionals. Fencing may be a well-suited activity to counteract fatigue, pain, and limited arm mobility.

**Method and analysis:**

The FENICE study is a mono-center, randomized clinical trial targeting women with BC stages I-III within four weeks from BC surgery. Participants in the control arm will receive the usual recommendations based on the good clinical practice guidelines. In the study arm, participants will be treated with the usual clinical and therapeutic recommendations together with APA and correct lifestyle suggestions.

**Objective:**

The primary objective of the study is to compare whether implementation of APA and healthy lifestyle in BC patient after surgery will result in an overall improvement of physical and mental status.

**Conclusion:**

Fencing and its early application in postoperative period may represent a feasible strategy to be implemented in the rehabilitation journey of BC patients.

**Ethics and dissemination:**

The study protocol FENICE has been approved by an Italian Ethics Committee on May 2023 (R.S 100.23 5^th^ May 2023).

## Introduction

Breast cancer (BC) is a growing global public health concern. Over time, different risk factors have been identified: alongside the genetic mutations (most commonly involving BRCA1 and BRCA2) implicated in hereditary form of breast and ovarian cancer, the most important risk factors for the sporadic form include personal and family history of BC, wide fertile window (related to early menarche, older age at menopause, first pregnancy after the age of 30 and nulliparity), the exposure to external sources of hormones (during hormone replacement therapy or using oral contraceptives), dense breast tissue and lifestyle based risk factors as alcohol consumption, tobacco, physical inactivity and sedentary lifestyle (1–4). The cancer screening programs in Italy comply with the guidelines established at European level, which are contained in the EU recommendation of December 16, 2003. These guidelines identify the three screening programs (breast, uterine and colorectal cancer) as the most effective cancer prevention measures (5). Despite the national cancer screening program launched since 2005, BC still affects many women in Italy. According to the latest AIRTUM (Associazione Italiana Registri Tumori) report, almost 56,000 new cases of BC have been diagnosed in our country in 2023, representing 30% of female tumors and 13% of all tumors regardless of gender (6, 7). At the same time the survival rate of patients has significantly improved (88% of 5-year survival rate) due to the recent treatments progress and the number of cancer survivors raised from approximately 2 million in 2006 to 3.6 million in 2020 (AIRTUM – Associazione Italiana Registri Tumori) (7). Improving prognosis due to early diagnosis and advances in therapeutic treatments has drawn the attention of health care professionals on disease related long-term side effects and on the multiple treatments BC patients must undergo (8). However, surgery represents the standard treatment for loco-regional BC, while radiotherapy (RT), antiblastic chemotherapy (AC), target therapy, immunotherapy and endocrine treatment are used in adjuvant and metastatic BC settings. During the past decades, conservative surgery (quadrantectomy) has become the first choice whenever possible, limiting mastectomy in selected cases only. Despite advances in procedures, surgery still has multiple detrimental effects, including pain, edema, and limited mobility (9–11). Posture very often appears to be compromised after mastectomy because the surgical scar limits arm mobility (e.g., internal rotation and shoulder droop are common, typically causing back pain) (12). In addition, the removal of lymph nodes (both the sentinel procedure and axillary lymph node dissection) is cited as a common cause of limited mobility and postoperative pain. Moreover, cancer treatments are also responsible of numerous long-term side effects as specified in **Table 1** (8, 13–18). Particularly, the use of aromatase inhibitors has been associated with possible risk of arthralgia and bone health worsening (19, 20). These aspects negatively affect the health-related Quality of Life (QoL) of BC patients (21, 22). BC patients also reported low levels of Work Ability (WA) and reduced outcomes in terms of employments status, employability, and fitness for work (23, 24). Some randomized clinical trials (25, 26) have demonstrated the benefit of regular and appropriate Adapted Physical Activity (APA) during and after BC treatment, particularly in terms of improved health status, strength, QoL and physical function, and fatigue reduction (**Table 2**) (35, 36). Moreover, two meta-analysis highlighted an inverse relationship between post-diagnosis APA and cancer-related mortality in patients with breast cancer compared to patients practicing low or no physical activity (37, 38). From another study emerged that patients with ER/PR negative cancer who had been physically active before the diagnosis had a significantly reduced risk for breast cancer recurrence compared to physically inactive patients (39). In early BC and in metastatic BC setting has been recently demonstrated that physical activity integration is able to improve general and physical well-being and mental health (40). Accordingly, these non-pharmacological treatments that alleviate long term side effects should be rated as a public health priority, as their role is crucial in improving overall survival (OS) and QoL in BC, cancer survivors included. For this reason, fostering APA and healthy lifestyle (including a balanced Mediterranean diet and weight management) should become an everyday purpose of healthcare professionals (41). In this context, APA as fencing has proven its affinity and efficacy as a supportive activity both during and after the treatment of BC patients (30, 35, 42, 43).

**Table 1 T1:** Side effects related to cancer treatments in breast cancer patients.

Late Side effects	Type of treatments				
	Chemotherapy	Endocrine therapy	Radiotherapy	Surgery	Target Therapy
**Arthralgia**	✗	✓✓✓	✗	✗	✗
**Bone health**	✓	✓✓✓	✓	✗	✗
**Cardiovascular disease**	✓✓	✗	✓	✗	✓✓✓
**Depression and anxiety**	✓✓✓	✓	✓✓	✓	✓✓
**Fatigue**	✓✓✓	✓	✓✓	✗	✓✓
**Lymphedema**	✗	✗	✓	✓✓	✗
**Metabolic disturbances**	✓	✓✓	✗	✗	✓
**Neurocognitive dysfunction**	✓	✗	✓	✗	✓
**Pain**	✓	✗	✓✓	✓✓✓	✗
**Peripheral neuropathy**	✓✓✓	✗	✗	✓	✗
**Respiratory impairment**	✓	✗	✓✓	✗	✓
**Sexual disfunction**	✓	✓✓	✗	✗	✗
**Shoulder limited mobility**	✗	✗	✓	✓✓	✗

✓✓✓Probably related (data from RCTs); ✓✓Might be related (data from RCTs with smaller samples); ✓Could be related (single-arm studies); ✗No sufficient data.

**Table 2 T2:** Beneficial effects of Adapted Physical Activity in cancer patients.

Sport/physical activity	Benefit	Reference
**Aerobic training**	**↓**CRF, **↑**health related QoL and physical function, **↓**anxiety, depression, **↑**sleep quality.	(27)
**Cycling**	**↑**QoL, **↑**Physical functioning, **↑**general health, **↑**vitality.	(28)
**Dragon Boat**	↑QoL, ↑Physical functioning, ↓fatigue.	(29)
**Fencing**	**↑**immunity function, **↑**adherence to therapies, **↑**health related QoL, **↓**CRF, **↓**anxiety, **↑**of the functional capacities.	(30)
**Resistance training**	**↓**CRF levels, **↑**health related QoL and physical function, **↓**lymphedema, **↑**aspects related to bone health.	(31)
**Rowing**	**↑**upper extremity and hip range of motion, **↑**lower and upper extremity strength, **↑**aerobic capacity and heart rate at rest and after prolonged effort.	(32)
**Swimming**	**↑**Flexion and external rotation of the operated arm.	(33)
**Walking**	**↓**Of the BMI, **↓**breast symptoms and in the arms, **↑**MS at the extremity of the upper limbs, **↓**of pain.	(31)
**Yoga**	**↑**joint mobility, **↑**muscle strength, **↑**QoL.	(34)

↓reduce; ↑ improve; CRF, cancer related fatigue; QoL, quality of life; BMI, Body mass index; MS, Muscle Strength.

Fencing can be a good activity to reduce fatigue, pain and limited arm mobility. As it is also a sport that naturally strengthens willpower, practicing fencing can have a positive effect on the attitude and psychological state of participants. Hence, the FENICE study protocol here described will assesses both physical and psychological outcomes.

## Research hypothesis and objectives

### Hypothesis

Adapted physical activity along with the introduction of Mediterranean diet and their early application in postoperative period may be a successful strategy to improve the physical and psychological health of BC patients underwent surgery (**Figure 1**).

**Figure 1 f1:**
[figure not shown]
Graphical summary of the primary aim of FENICE trial.

### Primary objective

The primary objective of the study is to compare whether implementation of an APA and healthy lifestyle (Mediterranean diet) will result in an overall improvement of physical and mental status including reduction in the number and severity of clinically relevant adverse events (AEs), in the study group compared with the control group during a 24-month enrollment period.

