### Design of FENICE trial

The FENICE study is a mono-center, randomized clinical trial targeting women with stages I-III BC within four weeks from surgery, conducted at the Breast Unit of Policlinico Tor Vergata Rome and Frascati Scherma ASD. The sequence of study and control group is randomized to minimize the influence of time-dependent variables. The participants, regardless of arm dominance, will be followed up by oncologists, radiotherapists, and surgeons according to the BC guidelines. All subjects participating in the study will undergo a sports medicine examination to objectify whether there are any alterations or diseases that pose a risk to the patient and to determine whether the patient needs to have additional tests and more specific examinations performed. For participants in the study arm only, APA consists of two fencing sessions (1 h/session) per week within 15 days of enrollment. The minimum number of sessions for the assessment of the primary endpoint is 48 sessions over six months up to a maximum of 96 sessions over 12 months (**Figure 2**).

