### Sample size

The hypothesis guiding the formal determination of the sample size proposes an expected improvement of at least 15 points in the mean DASH score. The DASH score is a valuable, pragmatic, and frequently utilized metric in individuals with various musculoskeletal disorders of the upper limb. Ranging from 0 to 100, it encompasses responses to 30 questions (https://orthotoolkit.com/dash/) An improvement of at least 15 points is considered clinically significant in enhancing functional ability. The statistical parameters are configured in a highly conservative manner, considering the non-pharmacological nature of the intervention (adapted physical activity) and the inherent inter-individual variability in response, particularly within the treated group (Group 1). Therefore, with alpha and beta errors set at 0.01, a standard deviation in Group 1 that is twice that of Group 2 (SD: 20 compared to 10), even exceeding the hypothesized difference (15 points), 56 patients per group are deemed necessary. Considering the enrollment capabilities of our group and potential physiological withdrawal of patients, the sample size has been increased to 150 total patients. The target population will be at least 18 years of age (of any ethnicity) with a diagnosis of non-metastatic breast cancer and already treated with surgery for the primary tumor. This total will be divided into two sub-groups by randomization in blocks of 75 patients each (intervention group, Group 1, and control group, Group 2). The first group will be distinguished by subjects treated with adapted physical activity rehabilitation and with correct lifestyle suggestions. The second group, on the other hand, will be characterized by standard care without physical activity rehabilitation or lifestyle suggestions.

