### Statistical analysis

The descriptive statistical analyses, the central tendency, variability, symmetry and kurtosis will be calculated, all accompanied by appropriate graphical representations. Regarding the inferential analyses, we will continue with the verification of the parametric and non-parametric hypotheses, respectively for the quantitative variables with parametric tests such as: Student’s t-test, Fisher’s F-test, etc. and for categorical variables using non-parametric tests such as: chi-square, Mann Wittney’s U, Fisher’s exact test, etc. Only results with p-values ≤ 0.05 will be considered statistically significant. Principal component analysis (PCA) will be adopted to explore the relationships among secondary variables and identify patterns of improvement related to the APA intervention (50).

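### The primary objective (overall physical and mental status plus adverse events) is not the outcome the trial is sized on (DASH alone), and alpha is 0.01 in the sizing but 0.05 in the analysis

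*Protocol article*

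**What the plan says.** Four places in the protocol article bear on what decides the trial.

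- **Primary objective.** The question is whether the intervention "will result in an overall improvement of physical and mental status including reduction in the number and severity of clinically relevant adverse events", and the comparison is to be made "in the study group compared with the control group during a 24-month enrollment period". No instrument, score, combination rule or analysis time point is given.
- **Design of FENICE trial.** This section speaks of a primary endpoint without naming it: "The minimum number of sessions for the assessment of the primary endpoint is 48 sessions over six months". The upper limit is 96 sessions over 12 months.
- **Sample size.** The calculation is built on "an expected improvement of at least 15 points in the mean DASH score". It is run "with alpha and beta errors set at 0.01", with SDs of 20 (intervention) and 10 (control). It gives 56 per group, raised to 75 per group. DASH is not called primary here or elsewhere in the text.
- **Statistical analysis.** Tests are listed by type of variable and none is tied to an endpoint. The threshold is general: "Only results with p-values ≤ 0.05 will be considered statistically significant".

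Table 4 (Data collection) assigns DASH to disability, the EORTC QLQ-C30 and BR23 to quality of life, MFI-20 to fatigue, HADS to anxiety and depression, IPAQ to physical activity, and a separate scale to oedema. The Secondary objective section places fatigue in the secondary tier.

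**The concern.** A sample size calculation fixes the error rates of one test. That test should be the one that answers the primary objective, at the alpha later used to judge it. Here the calculation fixes error rates for a difference in mean DASH, while the objective promises a conclusion on physical status, mental status and adverse events together. On Table 4's own mapping DASH covers disability and not mental status, and it is not an adverse-event measure.

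Two outcomes of the trial show what is at stake. If DASH is null and HADS or QLQ-C30 favours the intervention, the wording leaves room to report the primary objective as met. If DASH is positive and mental status is unchanged, the wording gives no verdict. Even for DASH alone, a p-value between 0.01 and 0.05 is significant under the analysis section but not at the level used for sizing.

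**Working it through.** **1. Reproduce the plan's figure.** Inputs from the Sample size section: difference 15, SDs 20 and 10, alpha 0.01, power 0.99, 1:1 allocation. Sidedness is not stated.

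Normal approximation, two-sided:

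n = (20² + 10²)(z₀.₉₉₅ + z₀.₉₉)² / 15² = 500 × (2.576 + 2.326)² / 225 = 53.4, so 54 per group.

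With the noncentral t (Welch or Student), two-sided, the answer is 56. One-sided calculations give 49 (normal) and 50 (t). The stated 56 is therefore a two-sided, t-based calculation for DASH, and it is correct for DASH.

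**2. Which parts of the objective does it cover?**

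| Part of the primary objective | Measure in the article | Covered by the sizing |
|---|---|---|
| Physical status | DASH among others; none designated | DASH only |
| Mental status | HADS, and in part QLQ-C30 | No |
| Number and severity of adverse events | Follow-up contacts | No |

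**3. Time frame and alpha.** The primary objective gives 24 months, and the design section gives six months as a minimum and 12 as a maximum for the primary endpoint. Alpha is 0.01 in the sizing and 0.05 in the analysis.

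**4. If any one favourable instrument could count as success.** The article does not fix how many outcomes make up the objective, so the count is an assumption. Table 4 names seven instruments. Five remain if MFI-20 is set aside (fatigue is secondary) and IPAQ is set aside (it measures activity behaviour).

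At least one p ≤ 0.05 in either direction, independent outcomes, no true effect:

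- 5 instruments: 1 − 0.95⁵ = 0.226
- 7 instruments: 1 − 0.95⁷ = 0.302

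At least one in the favourable direction, two-sided tests at 0.05 (0.025 on each side):

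- 5 instruments: 1 − 0.975⁵ = 0.119
- 7 instruments: 1 − 0.975⁷ = 0.162

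Correlation lowers these. For 7 instruments in either direction, simulation at assumed common correlations of 0.3, 0.5 and 0.8 gives 0.27, 0.23 and 0.15.

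**5. If all parts must improve.** The chance of a false overall claim is then no greater than that of a single component test, so there is no inflation. Power for the whole cannot exceed the lowest power among the parts. No effect size or SD is given for HADS, QLQ-C30 or adverse events, so that power cannot be computed and the 0.99 does not describe it.

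**6. If DASH is the single primary endpoint.** By the normal approximation with 75 per arm:

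SE = √(500/75) = 2.58; 15/2.58 = 5.81; power at alpha 0.01 = Φ(5.81 − 2.576) = 0.9994.

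The Welch calculation gives 0.9992. At alpha 0.05 both exceed 0.9999. If losses reduced each arm to 56, power at alpha 0.01 would still be 0.990 (Welch) to 0.993 (normal).

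**The case against.** The strongest reply is that DASH is implicitly primary. The design section speaks of one primary endpoint, the sample size rests on DASH, and the analysis section refers to secondary variables, which implies a primary one. Figure 1, described as a summary of the primary aim, is not available here and might name a measure. This is a fair reading of intent, and it is why the article cannot be said to establish that a null DASH result would leave the trial a success. It does not remove the conflict. If DASH is primary, the primary objective promises conclusions that DASH cannot give; if the primary objective stands, the sizing does not cover it.

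A second reply is that the full protocol or analysis plan may hold the multiplicity rules. That is accepted, and the lack of a multiplicity procedure for secondary outcomes is not part of this point. The point is that the stated objective, sizing variable, time frame and alpha disagree with one another.

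A reader might also infer that every questionnaire is a co-primary outcome and that the trial therefore carries a false-positive rate of 30% or more. The text does not support that. It does set a secondary tier, which includes fatigue; it does not say that any one favourable result suffices; and its wording can equally be read as requiring all parts to improve. The either-direction rates also count results that favour control, which nobody would present as success.

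**Conclusion.** The point holds. The stated alpha and power belong to a DASH comparison that is only one part of the stated primary objective. The alpha for that comparison is 0.01 in one section and 0.05 in another, its time point is not settled, and the article does not fix whether a null DASH result fails the trial.

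The size depends on a reading that the article leaves open. Under an any-one-suffices reading with an assumed 5 to 7 instruments, the false-positive chance is about 23–30% if independent, or about 12–16% counting favourable results only, and less with correlation. Under an all-must-improve reading, error is not inflated and the loss is the 99% power claim. These figures illustrate the ambiguity; they are not an established error rate for this trial. The sample size figure itself is sound for DASH.

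**What to change.** - Rewrite the primary objective so that the between-arm difference in DASH at one stated time point is the single primary endpoint, and name it as such in the design, sample size and analysis sections. Six months fits the minimum in the design section; the 24 months in the primary objective must be reconciled with whichever time point is chosen.
- State one alpha for the primary test in both the sample size and the analysis sections. Either 0.01 or 0.05 is affordable with 75 per arm.
- Move mental status (HADS, QLQ-C30) and adverse events to secondary objectives, and say that they cannot by themselves establish success.

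The cost is wording only: no more patients, visits or questionnaires. The downside is a narrower primary claim, about upper-limb function rather than overall physical and mental status. If the sponsor wants the broader claim, it needs a stated rule for combining the parts and a sizing that covers each of them.

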### Secondary objective

The secondary aim is to compare whether APA improves perception of cancer-related fatigue (CRF) and sleep quality (both measured via specific questionnaires), BMI, bone health, aerobic capacity, heart rate and serum lipid profile in the study arm. In addition, levels of Work Ability as well as health care provider and patient attitudes toward APA as adjunctive therapy will be assessed. Finally, the effect of adapted physical activity and a healthy diet on reducing the recurrence of the disease is being investigated.

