Adapted fencing includes offensive and defensive actions, which are performed considering the mobility of the shoulder. The primary (tierce = outside; quart = inside; fifth = head) and secondary blocks are therefore performed by patients with maximum mobility, without ever causing pain. Coordination, agility, and strength are encouraged during exercises between patients and during lessons with the fencing master. The adapted fencing lesson ends with a cool-down period. Since different subjects experience different physical outcomes for the cancer and the subsequent treatment, the program must address these individual needs while respecting safety principles. Therefore, rest and water breaks will be provided when necessary, and simplified or less strenuous movements will be suggested as alternatives for those who find parts of the workout too challenging or unsafe. In addition, participants are encouraged to use both saber and foil, also depending on which master is holding the training session. In any case, the weapons used will be adapted in material to avoid excessive strain or fatigue as stated above. Moreover, the courses and masters allow 12 participants per session with a maximum ratio of 1 master per 2.5 participants. During the study protocol, participants are also encouraged to follow healthy diet and adhere to the standards of the Mediterranean diet through the prescription of a personalized diet by a nutritional biologist involved in the project. Conventional bioelectrical impedance (BIA) testing to assess body composition is also planned during protocol follow-ups. To assess adherence to the Mediterranean diet, the Prevención con Dieta Mediterránea (PREDIMED) questionnaire will be completed both at the beginning and at the end of the study (49). The participants of the FENICE study will be followed up by several specialists before and during the APA period (**Figure 3**). This study was approved by the ethic board of the Policlinico Tor Vergata of Univeristy of Rome and the enrollment will start in September 2024 and the recruitment will take an 18 months’ time window for the inclusion of the expected 150 participants.

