**Figure 3 f3:**
[figure not shown]
Specialists composing the multidisciplinary team of the FENICE clinical trial. Each BC patient enrolled in the study arm will be evaluated and monthly followed up by specialists before and during the adapted fencing activity.

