
## Conclusion

In summary, the FENICE study protocol aims to introduce adapted Fencing and Mediterranean diet habits as suitable methods of postoperative BC rehabilitation. This innovative APA will be performed on 75 BC participants who will be closely followed by a multidisciplinary team of oncologists, physiatrists, nutritional biologists, radiotherapists, surgeons, cardiologists, gynecologists, psychologists, and Olympic fencing masters. We hypothesize successful adapted Fencing could improve BC patients’ physical status by reducing upper limb lymphedema and promoting a wider mobility of the operated limb. In addition to the physical improvement, the dietary recommendations (Mediterranean diet) together with workouts will positively affect patients’ lipid profile and the ratio of fat-free mass to fat mass. This study fits fully into the context of integrative and complementary medicine, which is increasingly finding a place in the care of the cancer patient. Together with the use of the most common biological CAMs (e.g., herbal products or botanicals, vitamins, minerals, probiotics, homeopathic products, and Chinese herbal remedies), also APA and proper nutrition (Mediterranean diet) fall into the large category of non-biological CAMs (53–56). The FENICE study protocol will be a further confirmation of an integrated approach to cancer treatment that requires multidisciplinary work and in-depth knowledge of this broad area.

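### The secondary aim asks what APA alone does, but the two arms also differ in prescribed diet and intensity of follow-up, so only the combined programme can be assessed

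*Protocol article*

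**What the plan says.** **What is asked.** The Secondary objective begins: "The secondary aim is to compare whether APA improves perception of cancer-related fatigue (CRF) and sleep quality". The same sentence goes on to lipids, BMI, heart rate, aerobic capacity and bone health, and does not mention diet. Statistical analysis plans a principal component analysis of the secondary variables to "identify patterns of improvement related to the APA intervention".

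**What the study arm receives.** Design of FENICE trial defines APA as two one-hour fencing lessons a week. The same section asks participants to "adhere to the standards of the Mediterranean diet through the prescription of a personalized diet by a nutritional biologist involved in the project". The Figure 2 caption and the group definitions under Sample size place the diet and lifestyle component in the study arm. The Figure 3 caption adds: "Each BC patient enrolled in the study arm will be evaluated and monthly followed up by specialists before and during the adapted fencing activity".

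**What controls receive.** Sample size describes standard care with neither the exercise nor the lifestyle component. Follow up visits sets three-monthly follow-up for controls. In the study arm comorbidities, co-medication, adverse events and BMI are checked monthly.

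**How the intervention is named elsewhere.** The Primary objective is "to compare whether implementation of an APA and healthy lifestyle (Mediterranean diet) will result in an overall improvement of physical and mental status". The Secondary objective itself ends with "the effect of adapted physical activity and a healthy diet on reducing the recurrence of the disease is being investigated". The Conclusion expects that "the dietary recommendations (Mediterranean diet) together with workouts will positively affect patients’ lipid profile and the ratio of fat-free mass to fat mass".

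**The concern.** The aim names one component as the cause, while randomisation assigns several together. BMI and lipids are the clearest cases, because an individually prescribed diet is a direct alternative explanation for a difference in either. For lipids and body composition the article itself credits diet as well as exercise.

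If the secondary aim is reported as worded, a difference in lipids, BMI, fatigue or sleep would be published as an effect of adapted exercise, although the diet or the closer follow-up could account for part or all of it. The Discussion hopes that the study will be a pilot for larger trials supporting national recognition of APA. A fencing-specific reading of these outcomes would give those trials a wrong starting point on which component matters.

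**Working it through.** **1. Is APA used as shorthand for the whole programme?** The text points against it. Design of FENICE trial defines APA by its fencing sessions. The Hypothesis and the Primary objective name diet separately from APA. Within the Secondary objective, the recurrence sentence names both components and the opening sentence names one.

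**2. How the arms differ.**

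| Component | Study arm | Control arm | Source |
|---|---|---|---|
| Adapted fencing | Yes | No | Design of FENICE trial; Sample size |
| Prescribed Mediterranean diet | Yes | No | Figure 2 caption; Design of FENICE trial; Sample size |
| Scheduled follow-up | Monthly for some items, three-monthly for the rest | Three-monthly | Follow up visits |
| Monthly specialist review | Before and during fencing | Not described | Figure 3 caption |

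No exercise-only arm, diet-only arm, factorial structure or contact-matched control is described.

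**3. What the contrast estimates.** Write *a* for the effect of fencing, *d* for diet, *f* for closer follow-up and *i* for any interaction among them. The expected difference between arms is

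Δ = a + d + f + i.

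This is one equation with at least three unknowns. The values a = Δ, d = f = i = 0 fit the data exactly as well as d = Δ, a = f = i = 0. More patients narrow the interval around Δ but do not separate its parts.

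**4. Is the sample size affected?** The plan's inputs are a difference of 15 DASH points, SDs of 20 and 10, and alpha and beta of 0.01. Sidedness is not stated.

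- Two-sided normal approximation: n = (20² + 10²)(2.576 + 2.326)² / 15² = 53.4, so 54 per group. One-sided gives 49.
- Two-sided Welch t calculation: power 0.9891 at n = 55 and 0.9904 at n = 56.

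The stated 56 per group is therefore reproduced. It concerns DASH under a comparison of programmes and does not depend on how the secondary aim is worded.

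**5. Outcome by outcome.** The Secondary objective puts lipids under APA alone, while the Conclusion puts them under diet together with workouts. The two statements cannot both describe what a lipid difference would mean. The listed fatigue, sleep, BMI, heart-rate, aerobic-capacity and bone outcomes come from the same contrast and have the same limit, though how plausible a diet or follow-up contribution is will vary among them.

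**The case against.** The strongest reply is that this is a legitimate trial of a package against usual care and that the documents mostly say so. The Hypothesis, Primary objective, Figure 2 caption, Ethical considerations and Sample size all name exercise plus diet or lifestyle. On that view the opening of the Secondary objective is loose wording. Much of this stands: the design needs no change, and the point concerns what may be claimed. It does not remove the point, because a stated objective fixes the claim to be reported, and this one separates APA from diet in one sentence and joins them in another.

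A reader might also infer stronger versions, which the documents do not support:

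- **That the main result is compromised.** Physical and mental status fall under the Primary objective, which is already framed as APA plus diet. The DASH and HADS comparisons are not touched by the wording of the secondary aim.
- **That controls get no specialist care.** Design of FENICE trial has participants followed by oncologists, radiotherapists and surgeons under guidelines, and Data collection describes contact by a nurse or data manager about every four weeks for participants generally. The arms differ in frequency and breadth.
- **That specialist contacts number 24 against 8 over 24 months.** Figure 3 ties monthly specialist review to the period before and during fencing, which lasts at most 12 months. Follow up visits counts monitoring of parameters, which is a different thing.
- **That the abstract claims efficacy for fencing.** The sentence "Fencing and its early application in postoperative period may represent a feasible strategy" is a hedged remark on feasibility.
- **That measuring dietary adherence mid-study would solve it.** An extra PREDIMED would describe the diet contrast but would not identify the fencing share. The planned timing at beginning and end is not an error.

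**Conclusion.** The concern holds for the opening sentence of the Secondary objective and for the matching phrase in Statistical analysis. As designed, the trial can say whether the combined programme differs from usual care on the listed secondary outcomes. It cannot say whether APA does.

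The size is qualitative: the APA share is not identifiable at any number of patients. The diet difference alone is enough for this, so the conclusion does not depend on how much weight is given to extra follow-up. It assumes that the prescribed diet goes to the study arm only. The diet sentence itself speaks of participants, but the Figure 2 caption and the group definitions under Sample size make that restriction.

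This is more than a clerical matter, since it changes what may be concluded. It leaves the design, the primary comparison and the validity of the randomised contrast intact.

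**What to change.** 1. Reword the opening of the Secondary objective along these lines: *to assess whether the combined programme (adapted fencing, prescribed Mediterranean diet and the closer follow-up that goes with it), compared with usual care, improves* the outcomes already listed. The item on attitudes towards APA can keep its wording.
2. In Statistical analysis, refer to patterns of improvement related to the combined programme.
3. Add one sentence stating that no fencing-specific or APA-specific effect will be claimed from this trial.

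**Cost.** Three text edits and a less specific claim. The 56 per group, the total of 150, the visits and the analyses stay as they are. Isolating APA would require a different design. For illustration only, a third arm at the same 56 per arm means 3 × 56 = 168 evaluable patients instead of 2 × 56 = 112, before any multiplicity adjustment and sized on DASH. That is not requested here.
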